#### Level 1: Individual Eligibility

Each individual participant within an adult cisgender SMM couple must meet the following individual-level eligibility criteria for the P3 pilot RCT: (1) currently identifies as male and was assigned male at birth (ie, cisgender); (2) be aged ≥18 years; (3) has access to a web-connected device (eg, smartphone, laptop, tablet, or computer); (4) lives in and plans to live in Lima, Peru, for the next 6 months; (5) reports being in a relationship with another cisgender, SMM partner and defines their partner as *someone they feel emotionally or romantically committed to above all others, such as a partner, husband, boyfriend, etc*.; (6) reports being in their relationship for a minimum of 3 months; (7) reports having had CAS with their relationship partner within the previous 3 months; (8) one of the relationship partners reports having had CAS with a casual sex partner in the same timeframe; (9) reports to having no history (ie, within prior 3 months and ever) of intimate partner violence; (10) reports not being coerced by their partner (or others) to participate in the study and related activities; (11) reports feeling safe in the current relationship to participate in the study and related activities; and (12) indicates willingness to test for HIV and other STIs at a local community–based organization at baseline and at 6 months after baseline.

Except for level 1 eligibility criterion number 8, individuals who do not meet all other above-mentioned criteria, will be deemed ineligible, thanked for their interest in the study, and provided a list of HIV and STI prevention resources and other health and relationship-oriented resources that are available in Lima, Peru. Individuals who meet all other criteria (other than number 8) will be prompted to complete an e-consent and enter complete contact information of themselves and their partner. Then, partner 2 will receive a study invite via WhatsApp, which will provide them with access to the eligibility screener and e-consent (if applicable). Level 2 eligibility criteria will automatically be evaluated once both partners complete the eligibility screener.

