#### Aim 3: Preliminary Efficacy of the Intervention

Using the 6-month pilot RCT, this research will examine the preliminary efficacy of the intervention on couples: (A) formation and adherence to an HIV and STI prevention care plan containing evidence-based strategies (eg, ART for U=U, PrEP, and routine testing); (B) formation and adherence to a detailed sexual agreement, (C) relationship functioning (eg, mutual constructive communication and self-efficacy of decision-making and working together), and (D) self-reported and biomarker-confirmed indicators of vulnerability vis-à-vis sexual behaviors (eg, CAS) and HIV and STIs. The pilot RCT will have an allocation ratio of 1:1 and block randomization with a block size of 2, with blocks defined by dyad serostatus. Outcomes A and B will be dichotomous, outcome C will be continuous based on a bounded Likert scales, whereas outcome D will be a count variable based on STI incidence, HIV incidence, and CAS.

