#### Primary Analyses

For outcomes A to D, descriptive statistics will be used to characterize the sample at each time point during the trial (baseline, month 3, and month 6), and by trial arm and couples’ HIV serostatus. Descriptive statistics will also be used to summarize cohort characteristics, relationship functioning variables, and sexual behaviors by the trial arm and by couples’ HIV serostatus. For couples, dyadic data will be calculated if there are no missing values from either partner. For continuous variables, couple-level mean variables will be generated by taking the averaged value from both partners’ scores. For within-dyad variables, couple-level differences will be generated by taking the absolute difference between each of the partner’s scores. Categorical dyadic variables will be generated based on whether both partners had the same or different answers. Two-sample 2-tailed *t* tests and chi-square tests will be used to evaluate differences between the immediate intervention arm and delayed intervention control arm for couple-level continuous and categorical independent variables, respectively, to further characterize the sample of couples in the trial.

An intention-to-treat (full analysis) approach will be used to determine the comparison between groups based on the initial randomization and using outcomes for all randomized individuals. The primary analysis will be to compare the proportions of couples with outcomes A, B, and D in the immediate intervention versus the proportions of couples with similar outcomes in the delayed control arm using a chi-square test with one degree of freedom in a univariate analysis from the corresponding contingency table. The efficacy rate will also be presented as the ratio between binomial proportions with CIs estimated through conventional methods used for the couple-level measurement.

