#### Intention to Treat

An intention to treat approach [55-57] will be used to include all enrolled participants in the analysis. Any individuals or couples lost to follow-up will be assigned an adverse outcome (for outcomes A, B, and D) to be able to include them in the analysis. For outcome C, those lost to follow-up will have to be excluded as the outcome is continuous and there is no cutoff to determine an adverse outcome. This follows an intention-to-treat analysis plan where all randomized individuals are included in the final analysis independent of their participation after baseline assessment, which will also help ensure that the benefit of randomization to balance confounders is retained.

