#### Power, Sample Size, and Effect Size Estimations

All power calculations were performed with PASS 2020 [59]. For the couple-level analyses, with 60 couples randomized to 2 arms (30 couples in each), for outcome C, we will have 80% power to detect a difference of 0.75 SDs of the mean relationship functioning measure (large effect [60]) using a linear model. For the dichotomous outcomes A and B, we will have 80% power to detect an absolute difference of 35% between the intervention and delayed conditions using a chi-square test. Our power increases for the outcomes analyzed at the individual level, where the correlation between individuals within a dyad must be considered (ie, the interdependence of individuals nested within dyads). For the incidence rate of outcome D assuming Poisson distribution, 30 couples in each arm will have 80% power to detect a difference of 50% rate reduction in STI rate (including HIV) between the intervention and delayed conditions at 6 months assuming a within-pair coefficient of variation between clusters at 0.25 and the intraclass correlation coefficient as high as 0.1 (even higher ICCs do not reduce rate reduction measure in a significant or meaningful way magnitude wise). For all analyses, the α level was set at .05 with 95% CI. This is a feasibility and acceptability trial that is only powered to detect large effects; however, if effect sizes are lower than hypothesized, we will use that information to properly power a large-scale RCT.

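### Outcome D is defined as a count and powered as an infection rate without CAS, but its primary test is a couple-level yes/no chi-square, so the stated 80% power does not belong to that test

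*Protocol article*

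**What the plan says.** - **Definition** (Aim 3: Preliminary Efficacy of the Intervention): A and B are dichotomous and C is continuous, whereas "outcome D will be a count variable based on STI incidence, HIV incidence, and CAS".
- **Primary test** (Primary Analyses): the plan will "compare the proportions of couples with outcomes A, B, and D in the immediate intervention versus the proportions of couples with similar outcomes" among delayed-arm couples, "using a chi-square test with one degree of freedom in a univariate analysis from the corresponding contingency table". The effect measure is also binary: "The efficacy rate will also be presented as the ratio between binomial proportions".
- **Power** (Power, Sample Size, and Effect Size Estimations): "For the incidence rate of outcome D assuming Poisson distribution, 30 couples in each arm" are said to give 80% power for a 50% reduction in the STI rate, HIV included, at 6 months. CAS does not appear in this statement, and no control-arm rate is given.
- **Loss to follow-up** (Intention to Treat): "Any individuals or couples lost to follow-up will be assigned an adverse outcome (for outcomes A, B, and D"). Outcome C is left out of this rule because it is continuous and has no cutoff that would define an adverse value.
- **Entry criterion** (Level 1: Individual Eligibility): each man "reports having had CAS with their relationship partner within the previous 3 months".
- **Timing**: the Aim 3 section places the between-arm comparison from baseline to month 3. Trial Study Design and the measures section place HIV and STI testing at baseline and month 6 only.

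**The concern.** One outcome is given three statistical types: a count, a Poisson rate and a proportion of couples. The rate leaves out a component (CAS) that the definition includes. The chi-square and the adverse-outcome rule both need a yes/no value, and none is defined. The reason given for keeping C out of the adverse-outcome rule, that it has no cutoff, applies equally to a count whose cutoff is not stated.

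Two things are at stake. First, a reader will take the 80% as the power of the planned primary test, and it is not. Second, the pilot is meant to supply effect sizes for sizing a later efficacy trial. If the analyst has to choose the meaning of D after seeing the data, that choice carries forward into the next sample size.

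The way CAS enters also matters. Every man has CAS with his partner at entry, and the prevention strategies that the plan names as examples (ART for U=U, PrEP, routine testing) do not require CAS to stop. If CAS and infection are merged into one yes/no outcome, a couple could manage its risk well and still count as an event.

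**Working it through.** **Inputs from the article:** 30 couples per arm, 1:1 allocation, alpha .05 (taken as two-sided), a 50% rate reduction, 6 months, between-cluster coefficient of variation 0.25. **Not in the article, so assumed:** the control infection rate, and the share of couples with CAS at follow-up. The planned 30 per arm is used because the power statement uses it.

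**1. The plan's own figures.** For C, 0.75 SD with 30 per arm gives 81% (t) to 83% (normal), against 80% stated. For A and B, a 35-point difference gives at least 79%, against 80% stated. Both are in order. The 80% for D cannot be reproduced, because no control rate is given. One can only solve for the rate that it implies.

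**2. Control rate implied by 80% power for the rate comparison.** Let m be the expected infections per control couple over 6 months, and m/2 in the intervention arm:

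n = (1.960 + 0.842)² × (m + m/2) / (m/2)² = 7.849 × 1.5 / (0.25 m)

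Setting n = 30 gives m = 7.849 × 1.5 / (0.25 × 30) = 1.57 infections per couple. Two men followed for half a year make one person-year, so this is 157 per 100 person-years. Adding the coefficient of variation of 0.25 and a small-sample allowance of up to two clusters raises m to at most 1.84.

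**3. The stated primary test at that rate.** Take *with D* to mean at least one infection in the couple, so P = 1 − exp(−m):

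- control: 1 − exp(−1.57) = 0.792
- intervention: 1 − exp(−0.785) = 0.544
- SE under the null: √(2 × 0.668 × 0.332 / 30) = 0.1216
- SE under the alternative: √[(0.792 × 0.208 + 0.544 × 0.456) / 30] = 0.1173
- power: Φ[(0.248 − 1.960 × 0.1216) / 0.1173] = Φ(0.08) = 0.53

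Exact binomial enumeration also gives 0.53. Other rates:

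| m (control, per couple, 6 months) | Rate comparison | Chi-square on any infection |
|---|---|---|
| 0.5 | 35% | 30% |
| 1.0 | 61% | 46% |
| 1.57 | 80% | 53% |

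For a halved rate, the chi-square stayed at or below about 55% at every m tried (0.06 to 2.2).

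**4. Conditional case: D as one yes/no composite of CAS or infection.** Let c be the share of couples with any CAS at follow-up, equal in both arms and independent of infection, and let p be the share with any infection. Then P = 1 − (1 − c)(1 − p). This is a separate scenario from step 3: infections fall from 40% to 20% of couples.

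| c | Control vs intervention | Power (approximate and exact) |
|---|---|---|
| 0 (infections alone) | 40% vs 20% | 39% |
| 50% | 70% vs 60% | about 12% |
| 80% | 88% vs 84% | 7-8% |
| 90% | 94% vs 92% | 5-6% |

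At the higher rate of step 3 (m = 1.57, halved), the composite has about 25% power at c = 50%, 10-12% at 80% and 3-8% at 90%.

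**5. Timing.** Infections are measured by test at baseline and month 6. The between-arm comparison ends at month 3, when no test is done. By month 6 the delayed arm has had access for 3 months and the immediate arm for 6. The infection comparison that the data allow is therefore earlier versus later access.

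**The case against.** The strongest reply has four parts.

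- **D may not be a single composite.** The aims and the Aim 3 section speak of indicators in the plural, and the Discussion separates self-reported behaviour from test results. A reader might infer that CAS swamps any effect on infections. The text does not establish that: it never defines a CAS-or-infection outcome, does not say which CAS counts, and gives no follow-up frequency. The entry criterion fixes CAS at baseline only. Assuming equal CAS in both arms also presumes no effect of P3 on CAS, which is itself a target. This part stands, so step 4 is conditional and shown as a range.
- **A cutoff is SAP detail.** A count can be cut at one or more, and an article may leave that out. That is fair for the cutoff alone. But the article does fix the test, the effect measure and the rule for losses, and these conflict with its own definition and power model. Step 3 already grants the cutoff of one or more, and the mismatch remains.
- **HIV is rare and half the planned men already live with it.** A reader might infer that the chi-square fails on small expected counts, or that these men should leave the denominator. Neither follows. The plan proposes no HIV-only chi-square, and men living with HIV can still acquire bacterial STIs. Only an HIV-specific analysis needs the restriction.
- **It is a pilot.** The article says that it is powered for large effects only, D is one of four outcomes in the third aim, and multilevel models are planned as secondary analyses. This limits the consequence. It does not justify quoting power for a different analysis.

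**Conclusion.** The inconsistency is in the text and needs no outside fact. D is a count in its definition, a rate without CAS in the power statement, and an undefined yes/no in the primary test and the loss-to-follow-up rule. The 80% does not describe the primary test. At the rate where the rate comparison would reach 80%, the chi-square on any infection has about 53%. That figure rests on a Poisson count, a halved rate, 30 couples per arm and an implied control rate of about 1.57 infections per couple over 6 months, which the article does not state.

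The further loss from merging CAS with infection is conditional on a single composite, with CAS equal in both arms. It is large across the range shown (about 12% down to 5-6%, against 39%), but it does not show that the plan as written swamps infections.

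**What to change.** 1. Take D out of the chi-square sentence and out of the adverse-outcome rule, and report infections and CAS as two outcomes.
2. **Infections:** use a Poisson or negative binomial model with a person-time offset and couple clustering. Include all men for bacterial STIs, and only men HIV-negative at baseline for HIV. State that tests exist only at baseline and month 6, so the contrast is immediate versus delayed access over 6 months and not P3 versus no P3.
3. **CAS:** use a negative binomial mixed model for the month-3 count, adjusted for the baseline count. This contrast is made before the delayed arm has access.
4. Restate the power for D for the analysis actually used, with its assumed control rate.
5. The Results section says that data collection ended in April 2024 and analysis is under way, so label the change as made after data collection.

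**Cost:** no new data are needed. D becomes two results instead of one, the restated power may be less favourable than 80%, and the late change has to be disclosed.

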## Methods

### Trial Study Design

The study design for the P3 DHI is a 6-month pilot RCT with an unmatched delayed control condition of 3 months. The pilot RCT for the P3 DHI is registered on ClinicalTrials.gov (NCT05873855). Assessments will occur every 3 months after the baseline assessment (at 3 and 6 months). Participants (ie, couples) will initially be blinded to which randomized condition they receive for the pilot RCT. Most study participation activities, including recruitment, eligibility screening, consent, enrollment, assessments, intervention, and exit interviews will occur on Zoom (Zoom Video Communications). During the pilot trial, participants will also undergo in-person HIV and STI testing at a local community-based organization at baseline and month 6. The planned sample size for enrollment is 60 adult cisgender SMM couples. The planned sample size will be balanced by dyad HIV serostatus and stratified by trial arm (ie, 10 seroconcordant negative, 10 serodiscordant, and 10 seroconcordant positive couples per arm). Florida International University (FIU) and Universidad Peruana Cayetano Heredia’s respective institutional review boards have approved the study protocol and all associated study activities.

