### Randomization

An allocated randomization block of 2:2, via an embedded algorithm within the P3 DHI, will be used to randomly assign couples to one of the following 2 intervention conditions following the baseline assessment: (1) an immediate intervention condition where couples will be able to use the P3 DHI for 6 months or (2) a 3-month delayed intervention condition where couples will be able to use the P3 DHI for the last 3 months of the trial. For ethical reasons, a delayed control condition was chosen for the trial study to provide all couples with access to the intervention while also permitting the ability to compare outcome differences between trial arms for the first 3 months of the pilot RCT. In sum, all couples in the pilot RCT will have access to use the P3 DHI for a minimum of 3 months, which will enable data pooling of the entire couple sample (N=60; ie, first 3 months for the immediate intervention condition plus the last 3 months with the delayed intervention condition). The study design will also enable the examination of long-term effects of the P3 DHI (ie, effects after 6 months of use) on outcomes and their use of the P3 DHI among couples randomized to the immediate intervention condition (n=30). Randomization will be blinded to couples but not to the study staff (administrators).

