### Pilot RCT Baseline and Follow-Up Measures

Items about evaluation will only be assessed during follow-ups after the participants receive the intervention. All other measures, items, and scales will be assessed at each time point throughout the trial, including baseline. In addition to screening for inclusion, the eligibility screener will capture a variety of demographic information from each participant including age, race, sex at birth, gender identity, sexual identity, highest education attainment, current employment status, has a primary health care provider, relationship type, relationship length, couple cohabitation, and couple HIV serostatus. Other demographic information will be captured at each data collection time point (ie, at baseline, months 3 and 6) to assess participant’s current living arrangement, type of health insurance, affordability to pay for health care or medication costs when needed in the past 3 months, as well as whether participants were in a situation that required them to reduce a meal size or skip a meal because of not having enough money for food in the past 3 months (social determinants of health). Skip patterns will be used accordingly for baseline and follow-up assessments at months 3 and 6. Multimedia Appendix 1 [24,27-49] provides a brief description of all other items and scales that will be assessed at each time point and how they relate to the constructs of CIT-HBC [13,14].

Beyond the General Anxiety Disorder 2-item, 5 other items will be used to capture aspects about anxiety and worry specifically related to sex and being in a relationship. The items include the following: “Do you ever feel like you are walking on eggshells around your partner? (Yes, No, I don’t remember)”; “In thinking about the past 3 months, how much did you worry or feel anxious about having sex with your partner? (0=never to 4=always)”; “To what extent did this anxiety stop you from enjoying sex with your partner? (0=not at all to 2=a lot)”; “In thinking about the past 3 months, how much did you worry or feel anxious about having sex with others, not including your partner? (0=never to 4=always)”; and “To what extent did this anxiety stop you from enjoying sex with others, not including your partner? (0=not at all to 2=a lot).” Skip patterns will be used for the above set of items such that some items may not be displayed depending on the participant’s response to the previous item.

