Longitudinal analyses will also be conducted [52-54], specifically for outcome C, relationship functioning variables, to explore changes over time and whether these changes differ by arm and by couples’ HIV serostatus. Specifically, generalized linear mixed-effects models (GLMMs) with SAS PROC GLIMMIX will be used to analyze the longitudinal data for outcome C from all 3 time points: baseline, 3 months, and 6 months after randomization. The analysis will fit a GLMM with fixed effects for time, a term for the pilot arm (immediate intervention vs delayed), and an arm-by-time interaction term. The GLMM will include random effects for the intercept and couple cluster (to account for within-couple correlation over time). Model fitting statistics will be used to determine the suitability of more parsimonious (eg, autoregressive) correlation structures and nonlinear effects for time. From the fitted GLMMs, the primary hypothesis will be examined by testing whether the coefficient of the group-by-time interaction term (the difference in slopes between immediate intervention vs delayed) is different from 0. The primary analysis will be performed at the couple level, with exploratory analyses performed at the individual level. For individual-level analyses, all models will use similar GLMMs with random effects to account for the intracluster correlation of couple members. We will also explore outcomes (A-D) at the individual level (n=120) by looking at each participant’s changes over time as secondary analyses of interest using multilevel models.

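### The primary chi-square for outcomes A, B and D ignores the serostatus groups used to block randomisation, and the baseline value, so it is conservative if serostatus predicts the outcome

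*Protocol article*

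**What the plan says.** The Trial Study Design section plans "10 seroconcordant negative, 10 serodiscordant, and 10 seroconcordant positive couples per arm". The Aim 3 section gives 1:1 allocation and "block randomization with a block size of 2, with blocks defined by dyad serostatus". Serostatus is therefore a design factor.

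The Primary Analyses section compares proportions of couples with outcomes A, B and D between arms "using a chi-square test with one degree of freedom in a univariate analysis from the corresponding contingency table", and adds a ratio of binomial proportions with a conventional interval. Neither serostatus nor baseline enters. The Aim 3 section nevertheless assesses efficacy through change in A to D and sets the arm comparison between baseline and month 3. Baseline values of the self-reported outcomes will exist: "All other measures, items, and scales will be assessed at each time point throughout the trial, including baseline".

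Outcome C is handled differently. A GLMM is fitted to baseline, month 3 and month 6 with "fixed effects for time, a term for the pilot arm (immediate intervention vs delayed), and an arm-by-time interaction term", and the interaction is the tested term.

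**The concern.** Blocking on a factor forces the arms to be alike on it, so the difference in proportions varies less from trial to trial. The plain chi-square takes its variance from the pooled proportion. That variance still contains the spread between serostatus groups which the design has removed. If the groups differ in outcome, the standard error is too large, the test rejects too seldom and the interval for the ratio is too wide.

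Outcome A makes such differences plausible, because two of the strategies named as examples, ART for U=U and PrEP, depend on serostatus. For outcome B the protocol offers no such link.

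Two things are at stake in a trial of this size: some power, and the precision of the effect estimates that the Aim 3 section wants for sizing a future efficacy trial.

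**Working it through.** **Inputs from the protocol.** Sample size: "with 60 couples randomized to 2 arms (30 couples in each". Three serostatus groups with 10 couples per arm in each. Significance: "the α level was set at .05 with 95% CI", taken here as two-sided. Effects at 80% power: 35 points for A and B, 0.75 SD for C.

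**Inputs assumed.** Control success rates by serostatus group, because the protocol gives none; a range is shown.

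**Reproducing the plan's figures.** For A and B, the least favourable pair 35 points apart is 32.5% and 67.5%.
- Null SE = √(2 × 0.5 × 0.5 / 30) = 0.1291.
- Alternative SE = √(2 × 0.325 × 0.675 / 30) = 0.1209.
- Power = Φ((0.35 − 1.96 × 0.1291) / 0.1209) = Φ(0.80) = 78.9%.

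Exact enumeration of the uncorrected test gives 79.7%. For C, a two-sample t test with 30 per arm and 0.75 SD gives 81.5%. Both stated figures hold.

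**Type I error by arithmetic.** Under blocking, the variance of the difference depends on the mean of p(1 − p) over the groups. The chi-square uses p̄(1 − p̄). If R is the ratio of the first to the second, the test in effect rejects when |z| exceeds 1.96/√R.

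| Control rates | mean p(1−p) | p̄(1−p̄) | R | 1.96/√R | Approx. type I error |
|---|---|---|---|---|---|
| 40/40/40% | 0.240 | 0.240 | 1.000 | 1.96 | 5.0% |
| 30/40/50% | 0.233 | 0.240 | 0.972 | 1.99 | 4.7% |
| 20/40/60% | 0.213 | 0.240 | 0.889 | 2.08 | 3.8% |
| 10/40/70% | 0.180 | 0.240 | 0.750 | 2.26 | 2.4% |

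**Simulation.** 200,000 trials per scenario, 10 against 10 couples in each group, comparing the uncorrected chi-square with the Cochran-Mantel-Haenszel (CMH) test:

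| Control rates | Type I error, chi-square | Type I error, CMH | Power at +30 points, chi-square | Power at +30 points, CMH |
|---|---|---|---|---|
| 40/40/40% | 4.9% | 5.0% | 66.2% | 66.3% |
| 30/40/50% | 4.5% | 4.8% | 66.4% | 66.9% |
| 20/40/60% | 3.7% | 4.9% | 67.1% | 70.7% |
| 10/40/70% | 2.3% | 5.1% | 68.5% | 79.8% |

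The simulated errors agree with the arithmetic. The stratified test stays near 5% and shows no loss of power in any row.

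**At the protocol's own 35-point effect**, with mean control rate 32.5%, power for chi-square against CMH is:
- 79.8% and 79.8% with equal groups;
- 80.1% and 80.4% with groups 10 points apart;
- 81.3% and 84.2% with groups 20 points apart;
- 83.5% and 90.8% at 5/32.5/60%.

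**Outcome C.** In 200 simulated mixed models with complete data, adding a serostatus main effect left the standard error of the arm-by-time term unchanged (0.1089 both ways). Baseline handling matters a little. At a single follow-up with assumed correlation 0.6:
- A change contrast has variance factor 2(1 − 0.6) = 0.80, so the difference detectable at 80% power is 0.736 × √0.80 = 0.66 SD.
- Baseline adjustment has factor 1 − 0.6² = 0.64, giving 0.736 × √0.64 = 0.59 SD.

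**The case against.** The strongest objection is that the size of the loss rests on assumed rates. Outcome A counts a plan built from evidence-based strategies, with routine testing also among the examples, and the intervention is serostatus neutral by design. Different components need not mean different success rates. The 68.5% against 79.8% contrast is the extreme end: adding 30 points to a 70% control rate puts one treated group at 100%. With groups 10 points apart the loss is negligible. All of this stands, which is why the result is a range that starts at zero.

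The trial also describes itself as one of feasibility and acceptability, powered only for large effects, and it reports outcomes by serostatus descriptively. That limits the weight of the point but does not make the unstratified test a better choice.

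A reader might infer more than the protocol supports:
- **That the test is invalid or the power claim wrong.** The error is on the conservative side, and the stated 80% reproduces.
- **That the outcome C model also ignores baseline and loses power by omitting serostatus.** Baseline is one of its three modelled time points, the tested term is a difference in change, and a serostatus main effect does not sharpen it.
- **That baseline adjustment would take outcome C from 0.74 to 0.59 SD.** That compares against a follow-up-only analysis, which is not planned.

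The stratified test does not use baseline status either. That part is met by the supporting model, and no gain can be calculated for it because the protocol gives no baseline rates or correlations.

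**Conclusion.** The point holds for the primary chi-square of A, B and D. The design blocks on serostatus and the primary test discards it, along with baseline status. Over assumed control rates from equal to 30 points apart, actual type I error runs from about 5% down to 2.3%. The power given up at a 30-point effect runs from 0 to about 11 points.

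The calculation assumes the planned 10 couples per group per arm, complete outcomes, and allocation within serostatus as the Aim 3 section states. The Randomization section describes the block differently ("An allocated randomization block of 2:2") and does not name serostatus there, so the two should be reconciled. With 20 couples per group, 10 blocks of two or 5 blocks of four both give 10 against 10. The article reports 74 couples enrolled but not their split by serostatus, so the figures describe the plan rather than the trial as enrolled.

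This is a worthwhile improvement in efficiency, not an error that threatens validity. For outcome C there is no demonstrated loss from omitting serostatus, only a modest optional gain from handling baseline differently.

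**What to change.** - **A and B:** make the month 3 primary test a Cochran-Mantel-Haenszel test stratified by the three serostatus groups, with a stratified risk ratio and risk difference and their intervals.
- **D:** do the same wherever it is analysed as a proportion, at the time point of that comparison.
- **Supporting analysis:** a logistic model with arm, serostatus and baseline status. This brings the primary comparison closer to the stated interest in change.
- **Plain chi-square:** keep it as a descriptive result.
- **C (optional):** constrain the arms to a common baseline mean, for a gain of about 0.66 to 0.59 SD at an assumed correlation of 0.6.

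Cost: no further data, since serostatus is recorded at screening. The stratified test still has one degree of freedom. The logistic model adds three parameters to the arm term, two for serostatus and one for baseline. The programming is trivial. As data collection has ended, the change should be fixed and dated before outcomes are compared by arm, or else reported as a post hoc refinement.
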